### Primary outcome measure

Percentage reduction in newborn deaths in Bungoma County between October 2015 and December 2018. This will be measured by comparing the number of newborn deaths at the nine project facilities (in the period of implementation), with the number of deaths at the same facilities in the similar period before the intervention; converted to percentage and aggregated by facility.

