## Abstract

**Background:**

Neonatal mortality is a major health burden in Bungoma County with the rate estimated at 31 per 1000 live births and is above the national average of 22 per 1000. Nonetheless, out of the nine sub county hospitals, only two are fairly equipped with necessary infrastructure and skilled personnel to manage neonatal complications such as prematurity, neonatal sepsis, neonatal jaundice, birth asphyxia and respiratory distress syndrome. Additionally, with more than 50% of neonates delivered without skilled attendance, in below par hygiene environments such as home and on the roadsides, with non-existent community based referral system, the situation is made worse. The study aims to evaluate the progress made by an intervention “Collaborative Newborn Support Project” geared towards reducing neonatal mortality rate by 30% between October 2015 and December 2018 in Bungoma County, Kenya.

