**Methods/Design:**

This intervention will take a quasi-experimental design approach with experimental and control sites. The project will involve pre- and post-intervention data collection with comparison group to assess intervention effects. The primary outcome will be the percentage reduction of neonatal mortality in Bungoma County. Secondary outcomes include; a) Percentage of mothers or care givers able to identify at least three danger signs in neonates in the project area, b) Proportion of neonates with complications referred to specialized neonatal centers, through the call center, c) Percentage of health providers in neonatal care units who adhere to expected neonatal standards of care (rapid and complete application of standard protocols), d) Percentage increase in neonates with severe complications in the specialized neonatal units and e) Percentage of neonates who stay in neonatal care units beyond 5 days.

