#### Selection of participants for the clinical observations of neonatal services

The sample size calculation is based on net change in the proportion of neonates who present with complications in health facilities. From the County HMIS data, it is estimated that a significant proportion of babies born with complications are missed out or only a few of them present to health facilities. In Bungoma County, currently only 21% present in health facilities. Through the Newborn collaborative support project, we seek to increase this by 50%, (21 to 32%). Given that births are 29,845 [16] and current situation is 21% presenting in health facilities we get a population of 6268 neonates. This means we get a sample size of 125 neonates for intervention and 125 for control group. Data collection tools such as questionnaires will be administered randomly amongst the selected cases. See Additional file 2.

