#### Rationale

More than 50% of neonates in Bungoma County are delivered without skilled attendance, in below par hygiene environments such as home and on the roadsides. This exposes the newborns to risk of infection among other complications. Often, these newborns fall ill and delay in seeking health services worsens outcomes. The call centre service, aims to streamline community based referral system, whereby, community based midwifes will report all deliveries in their locations to the call centre and the newborn mothers will be contacted and enrolled for follow up and provided with information to be able to make timely decisions for health seeking besides being sensitised on the availability of the special care units services near them.Newborn follow up after discharge is a critical component of care in sustaining wellness beyond the first month of life. A significant number of mothers may not be able to detect early symptoms of newborn illness such as sepsis or jaundice. The call centre service will actively prompt mothers on follow up after discharge to check out on symptoms and advise accordingly.Women on antenatal care follow up need information on how to nurture their newborns after delivery. Nonetheless, it has been noted that ante natal clinic attendance varies widely with drastic falls between second, third and fourth visits. Besides, since most of the health education sessions are held in the morning, mothers coming late do not attend and lose out on the education. This service will augment the ante natal care clinics in providing this information using calls and text messaging in addition to encouraging clinic attendance. The high mobile telephony penetration in the county makes this service feasible.The call centre service will provide a link between the community and the telehealth platform by providing community derived data that will inform project monitoring, strategies to enhance efficiencies in processes such as referral systems, community based midwifes engagements and newborn follow up outcomes.

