#### Interphase of telehealth platform and call center

The two innovations, telehealth and call center are key components in the success of the project. These will interphase as follows;The call center will promote community referral system linkage with the community based midwifes and the special care units, promoting utilization of the units. The telehealth platform will enhance the capacity of the clinicians in these units raising standards of care, user satisfaction and ultimately improving neonatal health outcomes.The call center will focus on follow up of the neonates born within the county health care system and without. The follow up data will be uploaded into the telehealth platform allowing the project pediatricians and clinicians understand the situation of the newborns in the community, respond to queries arising during follow up and streamline care and discharge processes in the special care units. See Fig. 1.

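### The primary outcome is labelled a county-wide reduction in newborn deaths but counts only deaths at nine hospitals, so it cannot confirm or refute the 30% county target

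*Protocol article*

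**What the plan says.** The Abstract (Background) sets the aim as "reducing neonatal mortality rate by 30% between October 2015 and December 2018 in Bungoma County, Kenya", from a stated county rate of 31 per 1000 live births. The Abstract (Methods/Design) says "The primary outcome will be the percentage reduction of neonatal mortality in Bungoma County". The section *Primary outcome measure* keeps the county label, "Percentage reduction in newborn deaths in Bungoma County between October 2015 and December 2018", and then fixes the measurement. It is made by "comparing the number of newborn deaths at the nine project facilities (in the period of implementation" and setting that count against its predecessor, "with the number of deaths at the same facilities in the similar period before the intervention".

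Other sections describe how much of newborn care happens outside hospital:

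- The call-centre *Rationale*: "More than 50% of neonates in Bungoma County are delivered without skilled attendance".
- *Selection of participants for the clinical observations of neonatal services*, on newborns with complications: "In Bungoma County, currently only 21% present in health facilities". The project hopes to raise this to 32%.
- *Selection of hospitals for the study*: 177 facilities in the county, 12 of them hospitals, nine of which take part.
- *Interphase of telehealth platform and call center*: "The call center will focus on follow up of the neonates born within the county health care system and without".

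**The concern.** The label and the measurement refer to different populations. The label covers every newborn in the county; the measurement covers deaths that happen in nine buildings. An analysis plan could not close this gap, because the data defined for the outcome leave out deaths elsewhere.

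If the outcome is reported under its present name, a fall in hospital deaths will be read as the same fall in county newborn deaths, and the 30% target will be declared met or missed on data that cannot decide it. This is separate from the choice of denominator or comparator. A hospital death rate with concurrent controls would still not be county newborn mortality.

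**Working it through.** **Inputs from the protocol article.** County rate 31 per 1000 live births (Abstract, Background). Births 29,845 a year (*Sample size determination*). Presentation of newborns with complications 21%, planned 32% (*Selection of participants for the clinical observations*). Target reduction 30%. No event count or power is given for the primary outcome.

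**The plan's own figure.** 29,845 × 0.21 = 6,267.45, which matches the stated 6,268 presenting neonates. The article applies the 21% to all births although the text describes it as a share of newborns with complications, so its exact meaning is uncertain.

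**What the target means for the county.** Expected deaths: 0.031 × 29,845 = about 925 a year. The target rate is 0.70 × 31 = 21.7 per 1000, or 0.70 × 925 = about 648 deaths a year.

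**From hospital to county.** Let f be the share of county newborn deaths that occur in the nine hospitals. Then

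county fall = f × (hospital fall) + (1 − f) × (fall elsewhere).

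The outcome observes only the hospital fall. The article gives neither f nor any measurement of the fall elsewhere. With a 30% hospital fall and no change elsewhere:

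| f (assumed) | County fall |
|---|---|
| 0.10 | 3.0% |
| 0.21 | 6.3% |
| 0.30 | 9.0% |
| 0.50 | 15.0% |
| 0.70 | 21.0% |
| 1.00 | 30.0% |

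**Is f close to 1?** Take 21% as the share of newborns with complications who reach any facility, and suppose that all newborn deaths arise among newborns with complications and that those who present die, if they die, in a facility. The facility share of deaths is then 0.21c / (0.21c + 0.79g), with c and g the case fatality inside and outside. Solving for the ratio, c/g = [f/(1 − f)] × (0.79/0.21). A share of 0.50 needs c/g = 3.8, a share of 0.70 needs 8.8, and a share of 0.90 needs 33.9. Sicker babies may well be the ones who present, so a ratio above 1 is believable; one near 34 is not. This is for all facilities together, and the nine hospitals can hold no more than that.

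**Direction of the error.** If deaths move out of hospital, they leave the count and read as lives saved. In the other direction, suppose presentation rises from 21% to 32% as planned, with the nine hospitals receiving their proportionate part and case mix and case fatality unchanged. Hospital deaths then change by 32/21 − 1 = +52%. Hospital case fatality would have to fall by 1 − 21/32 = 34% to hold the count level, and by 1 − 0.70 × 21/32 = 54% for the count to fall 30%.

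An illustration with assumed case fatality of 10% inside and 20% outside: deaths per newborn with complications go from 0.21 × 0.10 + 0.79 × 0.20 = 0.179 to 0.32 × 0.10 + 0.68 × 0.20 = 0.168. Total deaths fall 6% while hospital deaths rise 52%.

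**The case against.** The best defence is that hospital deaths are a legitimate endpoint for a project whose main component is equipped newborn units, and that the nine sites are high-volume hospitals, each covering a sub-county. That stands. It supports keeping the endpoint, but not calling it a county reduction.

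It may also be said that other data could supply community deaths. *Sources of data collection* lists the population within project sites, *Control group – Minimizing bias and contamination* has community workers report cases that never arrive, and the call centre yields follow-up and surveillance data. None of these is tied to the death count. The community-worker data are there to measure utilization.

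Several stronger readings are tempting, and the article does not support them:

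- *That f is 21% or 50%.* The 21% concerns presentation to any health facility, not deaths in the nine hospitals. The 50% concerns attendance at birth, and a baby born at home can die in hospital. Both serve only as points in an assumed range.
- *That even abolishing hospital deaths could not reach 30% in the county.* This needs a low f and no change elsewhere, yet the project sets out to change what happens elsewhere.
- *That the call centre's effect is mostly invisible to the endpoint.* It also refers sick babies to the special care units, and earlier arrival could lower counted deaths. How the effect divides is unknown.
- *That every death after discharge is missed.* The wording is deaths at the facilities, not deaths before discharge. A baby who is readmitted to a project hospital and dies there falls within it.
- *That the bias only flatters the project.* The planned rise in presentation pushes the count upward.
- *That nine of 177 facilities measures the gap.* Only 12 are hospitals; the rest are health centres, dispensaries and clinics.

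**Conclusion.** The concern holds as a mismatch between the named outcome and its measurement. The nine-hospital count cannot confirm or refute a 30% reduction in county neonatal mortality, because it omits newborn deaths at home, in other facilities, and after discharge without return to a project hospital.

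The size of the gap is unknown. Over an assumed f of 0.10 to 0.70, and with deaths elsewhere unchanged, a 30% hospital fall corresponds to a county fall of 3% to 21%. That f is not close to 1 is an inference from the article's figures on delivery and presentation, not a figure it states. The sign of the error is not fixed either: the 52% rise assumes constant case fatality and case mix and hospital deaths proportional to presentation.

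**What to change.** Rename the primary outcome as newborn deaths occurring at the nine project hospitals. In the Abstract (Background and Methods/Design) and in *Primary outcome measure*, state that this outcome cannot confirm or refute a 30% reduction in county neonatal mortality. This is a change of wording; its cost is a narrower headline claim.

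Optionally, from now on, record vital status and place of death for newborns whom the call centre already follows, and report these descriptively as a secondary outcome. The limits should be stated with it. The study has already begun, so earlier project time is not covered, and there is no pre-project comparator. The article gives the frequency of call-centre contacts but not how long they continue, so the length of follow-up would need to be set. Tracking individual babies would also have to be squared with the statement under *Privacy, informed consent and confidentiality* that no identifiers are used.

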## Background

Approximately 2.7 million new-borns die each year accounting to 43% of deaths of children under 5 years [1]. Maternal and new-born deaths were the focus of millennium development goals 4 and 5 which were not met by 2015 and are currently captured in the sustainable development goals [2, 3]. Kenya has a big neonatal mortality burden currently at 22 out of 1000 live births with Bungoma County at 31 per 1000 live births [4]. Major contributors to the morbidity and mortality challenge include poor new-born health coverage, low levels of perinatal care [5], adverse cultural practices including unskilled home deliveries, poor cord care comprising application of cow dung, lizard excreta, herbs and mud to ‘facilitate’ cord healing and early weaning. Additionally, the continuum of care from antenatal care to delivery and postnatal care and new-born health, is highly disjointed in most rural districts due to inadequate capacities (infrastructural, personnel and supplies) and strategies worsening the situation [6–8].

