### Anticipated impact

The project will contribute towards the two outcomes with activities linking as follows; 1. Increased access to and utilisation of quality neonatal health services since new-born special care units in 7 sub county hospitals will be set-up, introducing these services to the sub counties, establishing a mobile phone based follow up system for neonates will empower mothers to make timely health seeking decisions and avert complications. The community sensitization sessions will inform the members and stakeholders on availability of the services stimulating demand.

Secondly, the project will contribute to health system management strengthening to deliver quality neonatal health services because 90 medical staff will be trained, mentored and supported through a tele-health platform by paediatricians from Kenya Paediatric Association and Mount Kenya University. It is anticipated that this strategy will build the healthcare workers confidence in neonatal care and create a pool of trainers in the rural facilities. Moreover, repackaging and distributing 1000 copies of best practice neonatal clinical guidelines to facilities in the county will provide quick reference. A community referral system for neonatal health services will be enhanced working with community based midwives. Besides, it is anticipated that mothers and particularly with pre-natal challenges will choose to deliver in these facilities for better neonatal outcomes, raising skilled attendant deliveries.

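### The primary outcome is a change in the raw number of deaths at nine hospitals, so it mixes a change in risk with a change in how many neonates those hospitals receive, and it cannot stand for county mortality

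*Protocol article*

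**What the plan says.** The Abstract describes the project as "geared towards reducing neonatal mortality rate by 30% between October 2015 and December 2018 in Bungoma County, Kenya". The Background section gives the starting point as a rate, with "Bungoma County at 31 per 1000 live births".

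The Methods, under Primary outcome measure, label the outcome as a percentage reduction in newborn deaths in the county. They then define it as "comparing the number of newborn deaths at the nine project facilities (in the period of implementation") compared "with the number of deaths at the same facilities in the similar period before the intervention; converted to percentage and aggregated by facility". Neither live births nor admissions are named. By contrast, four of the five secondary outcomes are given an explicit numerator and denominator.

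The same document plans to change how many neonates these hospitals see, and which ones:

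- Selection of participants for the clinical observations: of complicated neonates presenting in health facilities, "we seek to increase this by 50%, (21 to 32"%).
- Anticipated impact: it is expected that "mothers and particularly with pre-natal challenges will choose to deliver in these facilities for better neonatal outcomes".
- Secondary outcome measures: a rise in severe-complication admissions is itself an outcome.
- Call center service (Operation) and the section on its link with the telehealth platform: sick newborns in the community are to be referred into the special care units.
- Call center service (Rationale): "More than 50% of neonates in Bungoma County are delivered without skilled attendance".

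**The concern.** A count of deaths is the number at risk multiplied by the risk. The aim concerns the risk, and the intervention is designed to move both. If the hospitals receive more neonates, the count can fall by less than the risk does, stay flat, or rise, even though each baby is safer. A baby who would have died at home and now dies in a new unit adds one to the primary outcome and leaves county mortality unchanged.

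The label is a second problem. The outcome is named for Bungoma County but counts deaths at nine of its 177 health facilities. Deaths at home and elsewhere do not enter, in a county where over half of births lack skilled attendance.

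At stake is the main result: as defined, it cannot separate better survival from changed attendance, and it cannot show whether the 30% county target was met.

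**Working it through.** **Inputs from the protocol article**

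- Births per year: 29,845. Share presenting: 21% now, 32% as target, described as a 50% rise (Selection of participants for the clinical observations).
- Target effect: a 30% fall in a rate that starts at 31 per 1000, which is 31 x 0.70 = 21.7 per 1000 (Abstract, Background).
- Expected deaths, sample size or power for the primary outcome: none stated.

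**The plan's own figures**

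29,845 x 0.21 = 6267.45, which agrees with the printed 6268 to rounding. The 50% rise also agrees: 0.21 x 1.5 = 0.315, printed as 32%. The volume ratio implied by the target is therefore 1.50 (unrounded) to 32/21 = 1.524 (as printed), with births and the frequency of complications held constant.

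**Formula**

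Let V be facility volume after divided by before, and r the relative fall in deaths per neonate presenting. Assume that deaths scale with volume and that case mix is constant. Then:

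- change in the count = V(1 - r) - 1
- fall in risk at which the count does not move = 1 - 1/V
- fall in risk needed for the count to show -30% = 1 - 0.70/V

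**Results**

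| V | How a true 30% fall in risk reads | Fall in risk that leaves the count flat | Fall in risk needed for a -30% count |
|---|---|---|---|
| 1.10 | -23.0% | 9.1% | 36.4% |
| 1.25 | -12.5% | 20.0% | 44.0% |
| 1.43 (= 1/0.70) | 0% | 30.0% | 51.0% |
| 1.50 | +5.0% | 33.3% | 53.3% |
| 1.524 | +6.7% | 34.4% | 54.1% |
| 2.00 | +40.0% | 50.0% | 65.0% |

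The baseline risk of death cancels. With an assumed fatality of 5%, deaths among the county's presenting neonates go from 313 to 329 at V = 1.50. With 20% they go from 1253 to 1316. Both are +5.0%.

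Under the same assumptions, deaths per neonate presenting would show -30% in every row.

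**The case against.** The strongest objection is to the size. The 21% and 32% refer to presentation in health facilities across the county, not at the nine hospitals. They appear only in the sample-size text for the clinical observations, and they are loosely defined: described as a share of babies with complications, yet multiplied by all births. Newly presenting babies might also be less sick, because the call centre aims at earlier care-seeking, or sicker, because severe cases are to be referred. All of this stands. V at the nine sites is an assumption, and the table shows a range rather than a forecast.

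A reader might infer that, on the plan's own target, a successful project will report about 7% more deaths. The documents do not support that. The sign reverses only if V at the nine sites exceeds 1.43, and no such V is given. A reader might also infer that the outcome is likely to flatter the project through falling attendance. The arithmetic allows it (V = 0.70 with unchanged risk reads as -30%), but everything in the plan points to rising use, so the bias expected from volume runs mostly against the project.

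It could be said that converting to a percentage supplies the denominator. Read with the outcome's own label, it is the percentage change between two counts. The protocol also plans to capture cases that fail to reach a facility, but for utilisation, not for the primary outcome. Finally, the gap is not detail left to an analysis plan: the definition is stated, and it is a count.

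**Conclusion.** The concern holds as a defect in the outcome definition. The aim is a rate and the measure is a count, and no other section repairs this. Unless V equals 1, the percentage change in the count differs from the percentage change in risk. For a true 30% fall in risk, the reading runs from -23% at V = 1.10 to +5% to +7% at V = 1.50 to 1.52. These figures are illustrative: they assume deaths proportional to volume and constant case mix, and they borrow the county-wide presentation target for the nine sites. The existence of the defect does not depend on any one V; its size and direction do.

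Separately, and without any assumption about V, a count at nine hospitals omits home deaths and deaths at other facilities, so it is not a measure of newborn deaths in Bungoma County.

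**What to change.** In the Primary outcome measure section, replace the count with facility neonatal mortality at the nine sites, using the same denominator definition before and after:

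- deaths before discharge among babies born at the nine hospitals, per 1000 live births there; and alongside it
- deaths among outborn neonates per 100 outborn neonates presenting or admitted. An inborn rate alone would leave out the referred babies whom the project targets.

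Keep raw counts as descriptive. Use the 15-score only for description, or for adjustment in periods where it was recorded: seven of the nine units are new and may have no baseline score. Label the result as mortality at the nine facilities and do not present it as the county rate. The 30% county reduction can remain the project's aim, but this measure cannot show whether it was reached.

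Cost: pre-period births and admissions totals must be abstracted from routine facility records. The documents do not confirm that these are available, so this should be checked first. The study is under way and registered, so the change needs a dated amendment and a registry update. The claim narrows from county to facility. Some case-mix shift will remain in the inborn rate as higher-risk mothers move to these hospitals, and should be acknowledged in the report.

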### Study design

This intervention will take a quasi-experimental design approach with an experimental and control site. The project will involve pre- and post-intervention data collection with one comparison group to assess intervention effects.

The study will be conducted at level 4 and 5 hospitals, each hospital having high volume of clients and covering a sub-county, all with similar maternal, newborn and child health indicators. Five hospitals will be the implementation sites while 4 hospitals will be control sites in a step wedge approach. The implementation sites will be selected purposely. The control sites will receive the full intervention after 1 year when the first set of comparison with the intervention site has been completed.

The 5 experimental site hospitals will receive a set of interventions which include: refurbishing of new born units, installation of equipment such as incubators, respirators, Ambu bags, and radiators. Establishment of a tele-health platform to enable free flow of information amongst clinicians and obstetricians, establishment of a call center for follow up of patients, training of health care providers in neonatology, and creating awareness amongst the community will be key cross cutting interventions, implying they will benefit the intervention site as well as control site. The control sites will not receive the main intervention benefits (equipped specialized newborn units) until after 1 year of implementation in the experimental sites.

The project will undertake a baseline, mid-term and end-line surveys. The step wedge design which allows for the measurement of process, outcome and impact indicators within each site (at different time points) will be used. The design also allows a comparison between different combinations of the intervention components.

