## Discussion

The innovation has four components supporting each other as follows;Operation of telehealth platform which is an innovative tool that supports teleconsultations between professional paediatricians and the clinical offices at different health facilities. The telehealth platform essentially provides solution to the challenge of inadequate professionals in the target area which currently has a single paeditrician serving a total population of approximately 1.7 Million people. It enables realtime consultations between the clinical officers and the paeditricians. In addition, it enables professionals in distant locatilities bridge the gap by providing required services. There are 5 professionals from Nairobi (a distance of approximately 500 Kilometers) serving the population in addition to the one resident professional. It works by having the clinical officers take images of newborns under stress and share the same alongside clinical notes with professionals for advice in realtime.Call centre enables the call centre attendants who are trained nurses to consult with mothers of newborns and offer advice aimed at shortening decision making to seek care. This handles the challenge of delayed decisions to seek medical care. The mothers will call the call centre and present any challenges they face with their newborns with an aim of getting advise to handle the danger signs that they may have noted with their newborns. This enables them to make decisions to seek required medical care on time. Community engagement involves sensitizing the community members especially mothers of newborns of improved facilities within their locality. In addition, the community members are trained on how to identify danger signs in newborns and take remedial action in good time. This approach reduces the delay in seeking care for the newborns when required. When the community is sensitized, it becomes proactive and make relatively good decisions concerning the health of their newborns.Measuring results (outputs and outcomes) will involve undertaking a baseline survey to establish benchmarks that will be used to gauge the success of the intervention. This survey will involve the community within the target area, clinicians in selected health facilities and administrators of the health facilities including the County government officials who are legally incharge of the health facilities in the region. Outputs and outcomes will be established through internal and external evaluations which will be conducted at midterm and endterm of the project intervention (see Table 1). These will consider the benchmarks established at baseline to establish change in the situation beased on the intervention. This evaluation will be exhaustive enough and objective to ensure that only results that can be attributed to the intervention will be included since there are many other efforts towards improving the helthcare of newborns in the target area.

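### The primary mortality outcome compares the nine hospitals only with their own past, with no concurrent control and no denominator, so it cannot support the attribution the protocol promises

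*Protocol article*

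**What the plan says.** Under Primary outcome measure, the protocol article names the outcome as "Percentage reduction in newborn deaths in Bungoma County between October 2015 and December 2018". It is obtained by "comparing the number of newborn deaths at the nine project facilities (in the period of implementation", and the comparator is "with the number of deaths at the same facilities in the similar period before the intervention; converted to percentage and aggregated by facility". The nine facilities are the implementation and control hospitals together. The definition contains no contrast between the two groups and no count of births or admissions.

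The design is described differently. The abstract announces "pre- and post-intervention data collection with comparison group to assess intervention effects", and Study design repeats this for "pre- and post-intervention data collection with one comparison group to assess intervention effects". The same section adds: "Five hospitals will be the implementation sites while 4 hospitals will be control sites in a step wedge approach". On timing it says: "The control sites will receive the full intervention after 1 year when the first set of comparison with the intervention site has been completed". It does not name the outcome of that first comparison.

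The Discussion undertakes to report only what is attributable to the project, and gives as its reason "since there are many other efforts towards improving the helthcare of newborns in the target area".

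**The concern.** Control hospitals are there to show what would have happened to mortality over the same calendar time without the main intervention. A comparison of each hospital with its own past has no such information. Any background change in newborn mortality, and any effect of the other programmes that the Discussion acknowledges, is counted as part of the project's result.

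The use of raw counts adds a second problem. The project intends to bring more sick newborns into these hospitals, so deaths there can rise or fall because the number of babies changes, with no change in risk.

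At stake is the causal reading of the main result. A reduction of the target size could be reported without the project having caused it, or a real benefit could go unseen.

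**Working it through.** The article gives no expected number of deaths and no background trend for this outcome, so there is no figure of its own to reproduce. The calculations below show the possible size and direction of the problem. The trends, volumes and effects in them are assumptions.

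**Inputs from the article.** October 2015 to December 2018 is 39 months, or 3.25 years. The target is a 30% reduction (abstract). There are five implementation and four control hospitals, and the controls wait 1 year (Study design). The intended relative increase in complicated newborns presenting to facilities is 50% (section on selection of participants for clinical observations).

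**1. Background trend alone.** If the earlier period is an equal 39-month window, the two windows are centred 3.25 years apart. With a background decline of s a year, a constant number of babies and a project with no effect, the apparent reduction is 1 − (1 − s)^3.25:

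- s = 2%: 1 − 0.98^3.25 = 6.4%
- s = 3%: 1 − 0.97^3.25 = 9.4%
- s = 5%: 1 − 0.95^3.25 = 15.4%

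If the earlier period is instead the preceding 12 months, the centres are 6 + 19.5 = 25.5 months (2.125 years) apart. The same declines then give 4.2%, 6.3% and 10.3%.

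**2. Rising use of the hospitals.** Suppose risk falls by 30% and the number of babies at risk in the hospitals rises by g. The count is multiplied by 0.7 × (1 + g):

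- g = 25%: 0.7 × 1.25 = 0.875, a 12.5% reduction
- g = 43%: 0.7 × 1.43 = 1.00, no visible change
- g = 50%: 0.7 × 1.50 = 1.05, a 5% increase

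The last case applies the intended 50% increase, on the assumption that hospital deaths scale with complicated newborns presenting. This bias runs against that in step 1.

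**3. Control time inside the implementation period.** If all sites start in October 2015, there are 9 × 39 = 351 hospital-months. Of these, 4 × 12 = 48 (13.7%) are control months without the equipped newborn units. With equal volumes, units opening at once elsewhere, and an effect that comes from the units alone, a true 30% effect would show as 0.30 × (1 − 0.137) = 25.9%. If the cross-cutting components also reduce mortality, this dilution is smaller, because the control hospitals receive them too.

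**4. What the controls could add.** In year 1, take equal baseline deaths per hospital, a 30% units effect in the five hospitals and none in the four. The nine-hospital before-after figure is 1 − (1 − s) × (5 × 0.7 + 4)/9. It equals 16.7% with no trend, 19.2% with a 3% decline and 20.8% with a 5% decline. The ratio of the change in the five to the change in the four gives 30% each time, provided that both groups share the trend.

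**The case against.** The best defence is that the outcome section only defines a measure, while the inference is planned under Study design, with a comparison group and a first comparison at 1 year. Per-hospital percentage changes could feed a five-against-four contrast, and a condensed article may leave that step to a fuller document. This stands in part. A reader might infer that the protocol abandons its control group, and the documents do not support that. The gap lies in the primary outcome definition, which fixes a historical comparator, and nothing elsewhere in the article ties the controls to mortality.

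Three other strong readings also go too far:

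- **That the outcome is one pooled figure.** Aggregation by facility may equally mean a percentage for each hospital. Neither reading brings in a concurrent control.
- **That control hospitals are untreated in year 1.** Study design and the later Control group section give them the cross-cutting components from the start; what they lack is the equipped newborn units. The Hypothesis concerns the whole package, so there is some basis for counting all nine hospitals as being in the implementation period.
- **That the measure must flatter the project.** The trend is assumed, and rising hospital use pushes the other way.

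The defence is also right that a controlled analysis has limits. Components that start everywhere at once are absorbed by calendar time. The two hospitals with some existing neonatal capacity are deliberately placed among the implementation sites, and the Study assumption section concedes that the groups may not be comparable. Hospital effects remove fixed differences between sites but not different trends.

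**Conclusion.** The concern holds in this form: the stated primary outcome uses neither a concurrent control nor a denominator, so it cannot carry the controlled assessment of effects or the attribution that the article promises. This is a matter of what the definition says. An analysis plan that used a controlled contrast for the primary outcome would depart from it.

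The size is illustrative. Assumed declines of 2% to 5% a year give 6% to 15% with equal 39-month windows, or 4% to 10% with a 12-month baseline, against a 30% target. Growth in hospital use of about 43% could hide a full 30% fall in risk. The net direction is therefore unknown. The fall from 30% to about 26% applies only to a units-only effect, with equal volumes and a common October 2015 start.

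**What to change.** Base any attributed effect on mortality on a controlled analysis:

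- Model deaths by facility and period (for example, quarter) with births or admissions as denominator, facility effects, calendar-time effects, and an indicator that switches on when each hospital's unit opens.
- Use inference suited to nine clusters.
- Make the year-1 change in the five hospitals against the change in the four the main contrast.
- State that this estimates the added effect of the newborn units and not of the cross-cutting package, and that it assumes common trends despite purposive selection.
- Keep the nine-facility before-after percentage as a descriptive measure of the county target, without causal attribution.

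**Cost.** The interval will be wider and the estimand narrower. Abstraction at all nine facilities through the project period is already planned, and the present definition already needs earlier death counts. Births or admissions for the earlier period are not documented as collected and would have to be retrieved from routine records.
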